## 3. Results

Recruitment for DUET spanned 8 October 2020 to 2 July 2021, and despite substantial overlap with the COVID-19 pandemic, met its accrual target of 56 partnered dyads within a 9-month period. To date, there have been no drop-outs; however, the trial is still in the field with completion of data collection anticipated within the next five months. Laboratory and statistical analyses will occur over the subsequent 6-month period.

Figure 1 details the study trajectory from self-referral or registry/wait-list ascertainment to randomization. Data suggest that for intervention RCTs like DUET, roughly 23 cancer survivors require contact for every participant enrolled. Granted, this number could be reduced to less than 20 if contact data in registries were current, but roughly 12% of cases were found to be deceased or had telephone and/or address information that was obsolete. Of those for whom contact is assumed, roughly 21% express interest in participating in the trial, but over one-third (37%) screen-out on various eligibility criteria with the leading causes for exclusion being normal or underweight status, already adhering to a healthful diet or regular exercise, or medical exclusions.

Of note, irregular computer use, or lack of Internet access was a rarely reported occurrence, with less than 2% being screened-out on this criterion. Moreover, while a substantial number of cancer survivors initially expressed interest, almost 20% were lost to follow-up afterward. This substantial loss to follow-up also occurred once enrollment became focused on partners; here loss to follow-up accounted for 28% of individuals identified either prior to consent or the baseline appointment. Additionally, the identification of a partner appeared to be a barrier since 42% of interested survivors were unable to enlist one.

DUET enrolled participants in Alabama, Illinois, Mississippi, North Carolina, and Tennessee. Table 3 provides the characteristics of the DUET cohort. The sample of survivors is comprised largely of individuals diagnosed with female breast cancer, though early-stage kidney, prostate, endometrial and ovarian cancer also are represented. Interestingly, 13% of supportive partners also reported cancer histories, again with most of these diagnoses being female breast cancer.

By and large, these are long-term cancer survivors more than five years (M = 67.5 months) out from diagnoses. Given the high representation of breast cancer (80%), it is unsurprising that most participants are female (86%). The age range is broad (i.e., 23–81 years) with a mean age of 58.4 years, and while most participants are employed (55%), one-third are retired. In addition, most (85%) acknowledged at least some college education, with a substantial proportion (43%) reporting annual incomes of at least $50,000 or refusing to answer this question. Minorities comprise almost 40% of the sample, with non-Hispanic Blacks (NHB) having the highest representation; however, very few participants are rural. While most dyads resided separately, over 40% cohabitated with their supportive partners (all of cohabitating partners were in spousal relationships). Both survivors and their supportive partners had average BMI’s falling in the range of Class I obesity (M BMI = 32).

Tests that compared the enrolled DUET cancer survivors (*n* = 56) to partners (*n* = 56) found significant differences for cancer diagnosis (*p* < 0.001), where the proportion of survivors with cancer (100%) was greater than the proportion of partners with cancer (13%), and for gender (*p* = 0.025), where the proportion of female survivors (86%) was greater than the proportion of female partners (68%).

Tests that compared the sample who responded with interest (*n* = 236) and ultimately enrolled in DUET (*n* = 56) to the larger pool who were unresponsive (*n* = 1029) and unenrolled (*n* = 1209) found no significant differences by rural (versus urban) residence or race/ethnicity (*p* > 0.10 for both); however, there were significantly higher response rates among survivors of breast cancer (and hence, females), as well as those who are younger (*p* < 0.05 for both). Though after screening, the only clear difference between enrolled participants versus the potential pool was the proportion of breast cancer survivors, which was significantly higher among enrollees (*p* < 0.0001).

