### 2.2. Participant Recruitment and Eligibility Screening

A two-step recruitment process was undertaken whereby initial enrollment efforts targeted cancer survivors, and once interest and eligibility were established, efforts were directed towards enrolling appropriate partners. Survivors of obesity-related cancers with 5-year cancer-free survival rates of at least 70% (i.e., localized renal cancer, and loco-regional ovarian, colorectal, prostatic, endometrial, and female breast cancers) [9]. Adult survivors of these cancers were identified through the UAB Cancer Registry, as well as through a wait-list of individuals who had previously expressed interest in lifestyle interventions and provided their contact email address or telephone numbers. Letters of invitation were posted to registry-ascertained cases, and telephone calls or email messages were placed to individuals on the wait-list. The Love Research Army (https://drsusanloveresearch.org/love-research-army, accessed on 27 September 2021) also initiated a series of email “blasts” to its members, and a recruitment website was established (https://duet4health.org, accessed on 27 September 2021). Finally, individuals not meeting eligibility criteria or disinterested in other ongoing cancer survivorship studies were apprised of DUET.

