Study staff provided telephone follow-up on recruitment mailings and contacts by placing up to six calls at various days and times. The study was explained and interested survivors were screened for eligibility. Inclusion and exclusion criteria were established to target survivors who were most in need and who could best benefit from a web-based diet and exercise intervention. Inclusion criteria were as follows: (1) BMI > 25 kg/m^2^ [10]; (2) vegetable and fruit intake <2.5 cups/day; (3) moderate-to-vigorous physical activity (MVPA) <150 min/week [11]; (4) completion of primary cancer treatment; (5) English speaking and writing; (6) educational attainment of 5th grade or higher; and (7) daily use of the Internet and mobile phone access. Exclusion criteria were few and limited to those who were already adhering to modified diets or enrolled in an exercise program, residing in assisted or skilled nursing facilities, or recently advised by their physician to limit physical activity and/or having health issues that might make participation in an unsupervised weight loss intervention unsafe (e.g., pregnancy, severe orthopedic conditions, end-stage renal disease, metastatic cancer or other cancers with poorer survival, paralysis, dementia, blindness, unstable angina, untreated stage 3 hypertension, recent history of heart attack, congestive heart failure or pulmonary conditions that required oxygen or hospitalization within 6 months) [12]. Once initial eligibility was established and cancer case status was verified by treating physicians of any self-referrals, the survivor was asked to identify a local support partner (preferably within a 10-min drive) and have them contact the research team for screening. Supportive partners were required to meet all inclusion/exclusion criteria, except for being a cancer survivor.

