For our initial statistical analyses that focus on determining potential demographic and cancer-type differences between enrolled DUET cancer survivors and partners, between cancer survivors who express interest in the DUET intervention versus those who refuse or are unresponsive, and those who enroll in the RCT versus those not enrolled, two-group t-tests are performed for continuous variables such as age, and chi-square tests are performed for categorical variables, such as gender, race/ethnicity, residence in a rural- or urban-classified county, and cancer-type. These analyses are now complete, and the results are presented in the next section—findings that are integral in assessing program interest and to appropriately generalize the main outcomes of this trial upon its completion.

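### The reported differences in response rate come from a pool that appears to include self-referrals, so recruitment channel as well as willingness to respond can produce them

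*Protocol article*

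**What the plan says.** Section 2.2 of the protocol article describes two kinds of recruitment. Registry cases received letters, and people on a wait-list of earlier volunteers were called or emailed. In addition, an outside research volunteer group "also initiated a series of email “blasts” to its members, and a recruitment website was established". Self-referral is expressly provided for: "cancer case status was verified by treating physicians of any self-referrals".

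Section 2.7 plans a comparison "between cancer survivors who express interest in the DUET intervention versus those who refuse or are unresponsive", and a second one of enrolled against not enrolled. Both use two-group t-tests and chi-square tests. No restriction to, or stratification by, recruitment channel is stated. The section says these analyses are complete and treats them as important for judging interest and for generalizing the trial's results.

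Section 3 describes one flow: "Figure 1 details the study trajectory from self-referral or registry/wait-list ascertainment to randomization". It sets "the sample who responded with interest (*n* = 236) and ultimately enrolled in DUET (*n* = 56") against "the larger pool who were unresponsive (*n* = 1029) and unenrolled (*n* = 1209"), and concludes that "there were significantly higher response rates among survivors of breast cancer (and hence, females), as well as those who are younger", with each p-value given as below 0.05. After screening, only the higher share of breast cancer among enrollees remains as a clear difference (p < 0.0001). The same section gives planning figures: "roughly 23 cancer survivors require contact for every participant enrolled", fewer than 20 if contact data were current, about 12% deceased or unreachable, and about 21% interest among those assumed to be reached.

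**The concern.** A response rate needs a denominator of people who were approached. Registry and wait-list cases have one: each was contacted, and those who did not reply can be counted. A self-referral arriving through the website or an email blast is seen only because that person was interested. Nothing in the article describes blast recipients who ignored the message, or website visitors who left, as part of the 1029. Self-referrals can then add to the interested side only.

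The comparison of 236 with 1029 then mixes two questions: whether some survivors respond more readily when approached, and whether the open channels reach a different case mix from the registry. If self-referrals are more often breast cancer survivors or younger, the test can reject with identical response rates among those approached. A reader planning a similar trial would conclude that other survivors are less willing, when the channels used might be the reason. The 21% interest figure is exposed in the same way.

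**Working it through.** **Step 1. Is there one pool?** From section 3:
- 236 + 1029 = 1265, and 56 + 1209 = 1265.
- Contacts per enrollee: 1265/56 = 22.6 (stated: about 23).
- Reachable: 0.88 × 1265 = 1113; 1113/56 = 19.9 (stated: fewer than 20).
- Interest: 236/1113 = 21.2% (stated: about 21%).

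All stated figures reproduce from this pool. All 56 enrollees are in it, so any self-referred enrollee is too. Since 0.12 × 1265 ≈ 152, the totals also imply that about 152 deceased or unreachable cases are counted among the 1029.

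**Step 2. How often can the interest test reject through channel alone?** The article's gender test (8/56 v 18/56, p = 0.025) is reproduced by a chi-square without continuity correction, so that version is used. Let m of the 236 be self-referrals with breast share s. The other 236 − m, and all 1029 unresponsive, have breast share r, so response is unrelated to cancer type among those approached. The values of m, r and s are assumptions. Simulated rejection at a two-sided 5%:

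| r | s | m = 10 | m = 20 | m = 40 | m = 60 |
|---|---|---|---|---|---|
| 50% | 80% | 6% | 11% | 29% | 57% |
| 50% | 95% | 8% | 18% | 57% | 91% |
| 65% | 80% | 5% | 6% | 11% | 19% |
| 65% | 95% | 6% | 11% | 31% | 62% |

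With the same case mix in both channels, rejection is about 5% whatever m is. For age (assumed SD 11 years), self-referrals 5 years younger give 10%, 24% and 48% with m = 24, 47 and 71. With self-referrals removed, rejection for breast cancer is 4.8% to 4.9%.

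**Step 3. Does the same explanation reach the enrolled comparison?** Let k of the 56 enrollees be self-referred, with r = 50%. The share of simulated trials giving p < 0.0001 for 56 v 1209 is:
- m = 40, k = 10: below 0.1%, for s = 80% or 95%.
- m = 60, k = 20, s = 95%: about 2%.
- m = 60, k = 30, s = 95%: about 25%.

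From Table 3, 45 of 56 enrollees had breast cancer. Against an unenrolled share of 65% that gives p = 0.018, so the reported p < 0.0001 implies an unenrolled breast share of about 54% or less. The r = 65% rows above therefore fit the article less well than the r = 50% rows.

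**Step 4. The planning figures.** Interest without self-referrals is (236 − m)/(1113 − m): 20.5%, 18.3% and 16.7% for m = 10, 40 and 60. It can only fall. Contacts per enrollee are (1265 − m)/(56 − k). With m = 40 this is 1225/56 = 21.9 if k = 0 and 1225/46 = 26.6 if k = 10, against 22.6 overall. It can move either way.

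**The case against.** The inputs that decide the matter are not in the text. Section 2.2 speaks only of any self-referrals, and the flow diagram, which may separate the channels, is not shown. With about 10 self-referrals, or similar case mix across channels, the distortion is negligible. That self-referrals bring no non-responders is an inference from how they enter, not a statement in the article. All of this stands, and it limits the point to what the tests can do.

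A reader might infer that channel explains the reported differences, including the excess of breast cancer among enrollees. The documents do not support that. Step 3 shows that channel alone would rarely give p < 0.0001 unless self-referrals made up roughly half of the enrolled survivors or more.

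A reader might also infer that the article's advice on recruiting elsewhere or stratifying accrual (section 4) falls with these tests. It does not. That advice answers the composition of the enrolled sample and covers rural residence, for which the tests found no difference. Nor are the planning figures shown to be uniformly too favourable: contacts per enrollee depend on an unknown k, and a whole-programme yield is a legitimate quantity.

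Finally, for generalizing the results, comparing all 56 enrollees with the full pool is reasonable. That also stands, provided it is read as a description of the sample.

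**Conclusion.** The point holds in a limited form. The matching totals of 1265 and the single described flow indicate that self-referrals were pooled with registry and wait-list cases, and the tests are unadjusted. Calling the result a difference in response rates therefore claims more than the comparison can show, because recruitment channel can also make it reject. In the scenarios tried, the rejection rate runs from near nominal (about 6%) to 91%. That range rests entirely on assumed numbers and case mix of self-referrals, and on the inference that they have no counted non-responders. It is not established that channel produced the breast cancer or age result. Channel alone is an unlikely source of the enrolled-versus-pool excess. The matter is minor: a completed, descriptive recruitment analysis, with no bearing on randomization, power or the comparison of weight between arms.

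**What to change.** - Rerun the interest comparison on registry-ascertained survivors who could be reached, leaving out the deceased and unreachable.
- Show wait-list cases separately, because they were selected on earlier interest, or stratify by channel, for example with a Cochran-Mantel-Haenszel test. Restricting to registry and wait-list together would leave some channel mixing.
- Give the number, cancer type and age of self-referrals, with no response rate.
- Give the 21% interest and the 23 contacts per enrollee by channel.
- Keep the comparison of all 56 enrollees with the full pool, worded as a description of the sample.

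The cost is a rerun on the recruitment records, assuming they record channel, and fewer cases in the tests.

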## 4. Discussion

To our knowledge, DUET is the first interactive web-based intervention aimed at improving body weight status, dietary intake, and physical activity among high-need survivors of obesity-related cancers and their supportive partners. As such, it represents a program that not only addresses the tertiary prevention needs of cancer survivors, but also serves to promote primary prevention among their friends and family members—a substantial proportion of whom are at higher risk due to common risk factors. In addition, DUET is unique from the perspective of capturing outcome data strictly using remote methodologies. Thus, it is among a new generation of trials in which the intervention is delivered, and the outcomes are assessed exclusively via remote means. The fact that we were able to meet our accrual target for this logistically challenging trial involving a 2-step process among both cancer survivors and partners within nine months, and during a pandemic when other cancer prevention and control trials are struggling (i.e., Unger et al. reports a decrease of 54% in enrollment during the same period [41]), is testimony to the fact that web-based approaches have appeal.

Remote delivered and assessed trials also have the ability to recruit participants broadly and thereby potentially increase the generalizability of findings. As such, DUET was able to engage participants residing in a broad swath of America, from Illinois to Alabama. Moreover, it attracted cancer survivors and supportive partners across a vast age range that extended from individuals in their second through eighth decades of life. It also enrolled a racial and ethnically diverse cohort, as supported by a minority accrual of almost 40%, thereby surpassing U.S. Bureau of Census statistics that suggest 31% for the mean age group of this sample (i.e., 58–59 years) [42]. Indeed, web-based trials remove several barriers that are commonly reported for both older and minority populations, such as transportation and time away from family or occupational commitments [43]. Furthermore, the concern that cancer survivors and their partners would not have Internet access nor adequate computer skills was unfounded based on our data that less than 2% of survivors screened-out on this criterion and there has been good uptake of the intervention to date. Albeit this percentage is far lower than the 18% computer-related exclusion that was recently reported by van der Hout and colleagues for a web-based supportive care intervention across a mixed sample of cancer survivors; however, recruitment for their Oncokompas trial occurred in 2016–2017 [44]. Given estimates indicating that there are on average 640,000 new users of the Internet each day globally (with sharp increases during the pandemic) [45], the concern that cancer survivors may be unreachable through web-based programs appears to be diminishing rapidly.

A much greater barrier to accrual was the identification of a partner in order to participate in this dyadic-based intervention. Forty-two percent of interested and eligible cancer survivors were unable to engage a supportive partner. While this proportion is lower than the 48% suggested by the DAMES trial, there was an expectation that expanding the criteria for a partner beyond just a biological child to include other family members, spouses, friends, and neighbors, would yield a far better response rate—it did not. Therefore, this is a key concern for dyadic-based interventions in the future, at least for those that are aimed at improving diet quality, physical activity and weight status among cancer survivors and their circles of friends and family members. That being said, the magnitude of change possible for dyadic interventions needs to be weighed against these logistical considerations. The fact that both the DAMES and Healthy Moves trials resulted significant improvements in vegetable and fruit consumption and/or weight loss with modest-sized samples suggests that although dyadic interventions are challenging, they still may be worth the effort [8,39]. The results for DUET will add substantially to this small body of research.

Of note, the considerable representation of dyad spouses within the DUET cohort and the relative ease with which the Healthy Moves cohort was assembled, suggests that the spousal relationship is perhaps the most fruitful to capitalize upon and engage potential participants [39]. Because the DUET sample is relatively evenly divided between survivor-spouse dyads versus dyads comprised of survivors and others, it will be one of the first (if not the first) to compare changes that occur in health behaviors and outcomes changes in these two different subgroups. While our study is likely to be underpowered in detecting significant differences, the descriptive data that result still will be helpful in supporting frameworks such as that proposed by Monterrosa et al. that identify and categorize the several different influences on food choices on various social and environmental levels [46]. Given that the spousal relationship and its inherent cohabitation affect food procurement and preparation, and other more far-reaching domains, we anticipate that intervention effects may be accentuated in this subgroup.

As stated, the outcomes of the DUET RCT are anticipated within the next calendar year. Given its potential to break new ground in the fairly small (yet growing) areas of dyadic interventions, as well as remote intervention delivery and evaluation, results should be of interest to researchers not only involved in cancer control, but also interventionists who implement diet and exercise interventions within a variety of patient populations and to prevent a multitude of chronic diseases. Strengths of DUET include its randomized controlled design, theoretically-grounded intervention, and attention to fidelity. As with all studies, DUET has limitations which include a significant overrepresentation of breast cancer survivors (many of whom are upper-socioeconomic), and few dyads with rural residence. These are common limitations that have been reported by other research teams [47,48,49]. To address these concerns, future studies might consider preferentially accruing from support groups that focus on other types of cancer and community cancer centers in smaller towns (rather than major tertiary oncologic care centers). Finally, and potentially as a last resort, future studies may need to stratify accrual by cancer type, socio-economic factors and/or rural/urban residence to assure adequate representation.

## 5. Conclusions

This paper provides an in-depth description of DUET—a theoretically grounded, dyadic-based lifestyle intervention for cancer prevention and control that is delivered and evaluated exclusively using remote technology. The report includes specific information on the overall protocol, intervention, and measures. Moreover, details are presented on the recruitment for this RCT which was successful in achieving its total accrual target with broad representation across the United States, and which also surpassed benchmarks for racial and ethnic representation.

